**6.4 Responsibility of investigational drug handling**

Xe (LenoXe®) will be supplied by Air Liquide Medical GmbH ([name]). Isoflurane (Forene®) will be supplied by the Abbott company. Both will be ordered by the central pharmacy (University Hospital Aachen; Director Dr. rer. nat. [name]; [name]). Department of Anesthesia, University Hospital Aachen will hold the responsibility for correct handling of the study drugs in accordance with the DGAI (German Society for Anaesthesiology and Intensive Medicine).

**6.5 Criteria for premature study termination due to the used study drug**

All used study drugs are drugs, which are used daily for anesthesia conduction. They are approved since several years in Germany, and were validated in many studies. They are safely used in the daily anesthesia conduction. Therefore, we do not expect any reasons for premature study termination due to the study drugs.

**6.6 Names of the other study drugs**

- Propofol
- Sufentanil
- Rocuronium
- Oxygen
- Medical air

**6.7 Responsibility for the other drugs**

All other drugs will be ordered and provided by the central pharmacy (University Hospital Aachen; Director Dr. rer. nat. [name]; [name]). Department of Anesthesia, University Hospital Aachen will hold the responsibility for correct handling of the study drugs in accordance with the DGAI (German Society for Anaesthesiology and Intensive Medicine).

**6.8 Concomitant therapy**

Concomitant therapy for comorbidities of the patient will be taken according to the suggestion of the investigator. There are no restrictions for concomitant therapies during the study.

**6.9 Prohibited drugs**

Other than the designated volatile anesthetics should not be used during visit 1 (general anesthesia).

**7 Outcomes**

**7.1 Outcome variables**

**7.1.1 Selection criteria and demographic data**

Following demographic data should be assessed:

- Birthdate
- Gender
- Height and weight
- Medical history, comorbidities and the respective medication, surgical history, smoking, alcohol use and/ or drug use, allergies
- ASA (America Society of Anesthesiologists) physical status
- Admission time-point
- Planned surgery time-point

**7.1.2 Primary outcomes**

The early postoperative renal function after Xe anesthesia compared to isoflurane anesthesia during PN, assessed by:

- GFR determination by cystatin C in serum, measured preoperatively and on the first 7 postoperative days. The maximum GFR decrease will be calculated as the difference between the preoperative baseline GFR and the nadir GFR within the first 7 postoperative days.

**7.1.3 Secondary outcomes**

The following secondary outcomes will be assessed in addition for the comparison of Xe anesthesia to isoflurane anesthesia:

- Measurement of the anesthesia and safety variables every 5 minutes and the determination of urine output at the end of surgery.
- Acute kidney failure determination according to the AKIN criteria, by measurement of the urine output every 6 hours until the second postoperative day, total urine output on the second postoperative day and determination of creatinine within the first 7 postoperative days or if earlier the day of discharge, respectively.
- Daily assessment of the safety data (creatinine, blood cell count, coagulation, urea in serum, transaminases and creatine kinase) until the 7^th^ postoperative day or if earlier the discharge day, respectively.
- Patients` vital data (blood pressure, heart rate, oxygen saturation) until the 7^th^ postoperative day or the discharge day (if earlier), respectively.
- Histological analysis with immunohistochemistry in paraffin sections and optional determination of HIF-1α in the tumor-free surrounding tissue via immunofluorescence staining.
- Determination of migration-inhibiting factor  (MIF) in serum.
- Determination of KIM-1 or NGAL in urine.
- Assessment of intraoperative blood loss.
- Assessment the anesthesia time until the beginning of the surgical ischemia (tumor resection time) and after the end of this surgical ischemia (defined by the termination of the tumor ground-treatment), until cessation of anesthesia. This will be assessed in collaboration of the investigator and the surgeons.
- Assessment of GFR and creatinine in serum after 3-6 months postoperative.

**7.2 Outcome measures**

Investigator I will assess inclusion criteria and demographic data during visit 0. Intraoperative data will be assessed, documented and analyzed by investigator II during visit 1. Blinded investigator I will assess the remaining secondary outcomes postoperatively until the 7th postoperative day or discharge day (if earlier), respectively. We will maintain two case report forms (CRFs) with all patient data, to assure blinding procedure. One CRF will include visit 0, 2-10, the other one for visit 1. All data outside of range will be validated by the investigator and marked as clinically significant (cs) or not clinically significant (ncs). Each clinically significant value will be considered as an AE and documented in the adverse event section.

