**1.2 Rationale**

The noble gas xenon (Xe) is approved since 2005 in Germany and 2007 in Europe for clinical routine use as an inhalational anesthetic. It is used for balanced anesthesia together with opioids for adult American Society of Anesthesiologists (ASA) ≤III patients. Different experimental *in vitro* and *in vivo* models were able to demonstrate the neuroprotective and cardioprotective effects induced by Xe treatment [12-15]. Both pre- and post conditioning protocols were effective [16-17]. Nephroprotection by Xe was recently shown in an *in vivo* IRI model and *in vitro* model of glucose deprived injury in human tubular kidney cells [18-19]. Both studies found an increased expression of hypoxia inducible factor-1α (HIF-1α) in the Xe treated cells or kidneys of the animals [18-19]. The nephroprotective effect was abolished by inhibition of HIF-1α activity [18]. Further nephroprotective effects showed Pype et al. Xe-saturated cold storage solutions reduced the ischemia-reperfusion injury after 6 hours of cold ischemia in a rat model of renal transplantation [20]. Animals with Xe-treated kidneys showed better creatinine-clearance after 7 and 14 days and decreased excretion of albumin in urine, which shows the tubular injury [20]. Clinical data from our study group revealed a better renal function in patients undergoing cardiac surgery after Xe anesthesia [21]. Furthermore, we could show that IRI on cardiac surgery patients leads to an enhanced release of macrophage migration- inhibiting factor (MIF) in serum. MIF was associated with an enhanced antioxidative capacity and less postoperative renal failure [22]. Therefore the influence of Xe compared to isoflurane on MIF should be examined in the present study. Beside the experimental organ protective effects, Xe is an effective anesthetic with favorable hemodynamic properties with blood pressure stability and low heart rates [10-11]. Other anesthetics like isoflurane, desflurane, sevoflurane and propofol usually show low blood pressures; with the need of catecholamines during anesthesia. Both low mean arterial pressures as well as the vasoconstrictive drugs like norepinephrine have additional negative influence on the renal function. This could lead to a beneficial risk-benefit ratio for Xe.

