**3.2 Randomization**

The randomization sequence will be generated computer-based by an independent biometrician. Patients will be randomly allocated according to a computer-based algorithm into the two groups Xe or control. Allocation concealment will be achieved by sequentially numbered, sealed opaque numbered envelopes, which will be kept safe until randomization of the single patients. Patients will be enrolled and pseudonymized with sequential increasing numbers by an investigator after obtaining written informed consent. All data will be collected under this pseudonymized number and only the biometrician and the monitor will have access to the randomization sequence, which includes the allocated treatment (Xe or control). The patients, the outcome-assessing investigator and the surgeon will be blinded (the ventilator will be the same for all patients to prevent accidental un-blinding). Only the second investigator, who performs the anesthesia and the intraoperative data assessing study-nurse, cannot be blinded.

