**5.3 Visits**

All patients will undergo a maximum of 11 visits. Visits 0 and 2-10 will be performed in a blinded manner by investigator I. Only investigator II and the study nurse will perform the intraoperative visit un-blinded, due to the special kind of Xe anesthesia administration.

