**8.1.2 Clinical safety variables**

- Systolic and diastolic blood pressure and heart rate will be assessed and documented every 5 minutes from entering the operating room until discharge from the operating room and every 15 minutes in the PACU.
- ECG will be measured continuously in the operating room and PACU. Investigator II will register clinically significant ECG deviations. They will be entered in the respective adverse event section, including the severity and treatment of the AE.
- Oxygen saturation will be assessed by pulse oxymetry continuously in the operating room and PACU. It will be documented every 15 minutes.
- Investigator II will assess the respiratory variables by Felix Dual® every 15 minutes during anesthesia (FiO_2_, saturation, FeO_2_, CO_2_et, Respiratory minute volume, respiratory rate, airway pressures).
- Cuff pressure will be checked every 5 minutes during ventilation and adjusted to 25-30 cmH_2_O.
- Urine output and blood loss will be measured every hour and at the end of surgery.
- Incision-suture time, warm ischemia time corresponding to the direct tumor resection time until termination of the tumor ground-treatment, will be assessed in collaboration with the surgeons.
- Occurrence of AEs and SAEs will be assessed GCP-conform during each visit and documented in the respective section of the CRF.

**8.2  Safety measures during visit 0, 2-9**

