8.4 Adverse events (AE)

An adverse event (AE) is any untoward medical occurrence in a patient or clinical investigation subject administered a pharmaceutical product and which does not necessarily have a causal relationship with this treatment. An adverse event (AE) can therefore be any unfavorable and unintended sign (including an abnormal laboratory finding), symptom, or disease temporally associated with the use of a medicinal (investigational) product, whether or not related to the medicinal (investigational) product. This can include diseases or symptoms, which occur or deteriorate after patient inclusion into the study (GCP-V §3 section 6). If the patients themselves or study personnel do not report AEs, they will be assessed by meticulous clinical examination, assessment of safety variables and a non-suggestive patient interview by the investigator. Furthermore, they will be documented thoroughly. If an investigator assumes an AE, he has to take all measures to make a diagnosis and the corresponding medical treatment. Patients will be observed and treated according to the medical need, until disappearing of symptoms, normalization of the laboratory variables and finding of a sufficient explanation for the observed event. Patients remain in-hospital until they meet the department and hospital standards for discharge. In addition, the investigator will evaluate, the dependence of the AE and the study treatment. The following will be documented in the CRF:

- Kind of AE (signs, symptoms or disease)
- Differentiation (serious/ not serious)
- Date of onset and end
- Intensity
- Causality to the investigational product
- Measures with regard to the study treatment or measures for recovery or improvement of patients` well-being
- Outcome of the event.

Intensity of the symptoms or the adverse event, respectively will be documented as follows:

- **Mild:** Perception of mild symptoms. Symptoms can be ignored easily or disappear, if the attention is diverted to other things.
- **Moderate:** Symptoms cause discomfort, but they are tolerable. They could not be ignored and compromise concentration.
- **Severe:** Severe symptoms, compromising the performance of usual activities.

Sponsor has to be informed about all AEs.

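### At Visit 1 the step that turns a value into an adverse event is an unblinded judgement, and the symptom-based intensity scale cannot grade events under anesthesia or symptom-free laboratory values

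*Protocol*

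**What the plan says.** **Who is unblinded.** Protocol 3.2: "Only the second investigator, who performs the anesthesia and the intraoperative data assessing study-nurse, cannot be blinded". Section 5.3 confines this to one visit: "Only investigator II and the study nurse will perform the intraoperative visit un-blinded, due to the special kind of Xe anesthesia administration". Visits 0 and 2-10 are done by blinded investigator I.

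**Who judges Visit 1 data.** Section 7.2: "Intraoperative data will be assessed, documented and analyzed by investigator II during visit 1". Visit 1 has its own CRF, separate from investigator I's. Section 5.3.2 places the PACU within Visit 1 and has investigator II document the data.

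**How a value becomes an AE.** Sections 7.2 and 8.3 have the investigator mark each out-of-range value as clinically significant or not. Then "Each clinically significant value will be considered as an AE and documented in the adverse event section". Section 8.3 adds that evaluation follows hospital SOPs and a reference table, neither of which is reproduced. For ECG the assessor is named in 8.1.2: "Investigator II will register clinically significant ECG deviations", with severity and treatment to be entered.

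**How an AE is graded and attributed.** Section 8.4 gives causality to the investigator and defines three grades by what the patient feels or can do. Moderate, for example, reads "Symptoms cause discomfort, but they are tolerable. They could not be ignored and compromise concentration". Mild refers to symptoms that can be ignored, severe to usual activities. There is no other scale.

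**The concern.** Two defects meet at Visit 1.

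The first is ascertainment. A reading creates an AE only if someone judges it significant, and during exposure to the study gas that person knows the arm. The protocol also states an expectation. Section 1.2 says "Xe is an effective anesthetic with favorable hemodynamic properties with blood pressure stability and low heart rates" and describes other anesthetics, isoflurane among them, as usually giving low pressures with catecholamine need. Section 1.3 makes hemodynamic stability one of two routes by which xenon might help. After Visit 1 the same judgement is made blinded.

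The second is grading. A patient under general anesthesia reports no discomfort and has no concentration to lose, yet 8.1.2 requires a severity for intraoperative ECG events. The same gap affects symptom-free laboratory values at any visit, which 7.2 and 8.3 turn into AEs. Without a usable definition, the grade is whatever the assessor chooses.

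At stake is the reading of an AE table. A difference between arms in intraoperative AEs, their grade or their attribution could reflect marking rather than harm.

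**Working it through.** The protocol states no figure on this point, so there is none to reproduce. The check is mainly a reading of the sections together.

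1. *Is the Visit 1 mark unblinded?* For ECG, yes, by name (8.1.2). For pressure, heart rate and saturation, 7.2 and 8.3 say only the investigator. Investigator II does the visit (5.3), documents it (5.3.2), assesses its data (7.2) and has a separate CRF, so the mark falls to investigator II by inference. The study nurse is also unblinded. No blinded review of Visit 1 events is described.
2. *Does the scale fit?* Each grade in 8.4 needs a perceived symptom, attention, concentration or usual activity. None can be observed under general anesthesia or read from a laboratory value without symptoms. The scale can be used for awake PACU patients with symptoms.
3. *What does not depend on the mark?* Pressure and heart rate are documented every 5 minutes in the operating room and every 15 minutes in the PACU, and saturation every 15 minutes (8.1.2). Section 7.1.3 lists the 5-minute anesthesia and safety variables as a secondary outcome for the comparison of arms. The primary GFR endpoint is laboratory based.

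**Illustration of possible size.** Only n = 25 per arm comes from the protocol (9.1). The true incidence q, equal in both arms, and the marking probabilities m are assumptions.

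- AE rate in an arm = q × m.
- False difference = q × (m₁ − m₂).
- Chance of p ≤ 0.05 = sum of the binomial probabilities of all pairs of counts that a two-sided Fisher test rejects.

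| q | m₁ / m₂ | AE rates | False difference | Fisher p ≤ 0.05 |
|---|---|---|---|---|
| 40% | 90% / 90% | 36% / 36% | 0 | 2.7% |
| 40% | 90% / 70% | 36% / 28% | 8 points (2 of 25 patients) | 5.1% |
| 40% | 90% / 60% | 36% / 24% | 12 points (3 of 25) | 8.8% |
| 60% | 90% / 90% | 54% / 54% | 0 | 3.2% |
| 60% | 90% / 70% | 54% / 42% | 12 points (3 of 25) | 10.0% |
| 60% | 90% / 60% | 54% / 36% | 18 points (4.5 of 25) | 19.4% |

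A pooled z-test rejects more often: 9.9-16.3% at 90%/70% and 15.9-28.5% at 90%/60%, against 5.7-6.4% with equal marking. The protocol fixes neither test for AEs. Swapping the arms reverses the sign and leaves the sizes unchanged.

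**The case against.** The strongest reply is that the protocol defines no AE comparison that could be biased. Section 2.3 lists AEs and SAEs as additional safety data, the comparative outcomes in 7.1.3 contain no AE count or grade, and 9.3 leaves other variables to descriptive and exploratory analysis. The hemodynamic hypothesis can be examined on raw readings that nobody marks. This stands and limits the point to AE reporting. It does not rescue the AE table, and the rule, the assessor and the scale are fixed in the protocol and govern CRF entry, so a later SAP could not recover blinded grades.

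Other replies stand in part:

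- The SOPs and reference table in 8.3 may narrow the discretion. They are not shown, so by how much is unknown.
- Blinding the anesthetist is impossible, as 3.2 acknowledges. The point does not ask for it.
- SAEs follow the outcome criteria of 8.5, not the symptom scale.
- Postoperative laboratory values are judged by blinded investigator I, so for them only the scale is at fault.

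A reader might infer from 1.2 and 1.3 that the bias favors xenon. Those sections show an expectation, not how investigator II will mark values. A reader might also count the 5-minute readings and conclude that most AE sources are judged unblinded. That would leave out the daily laboratory panel, and serial readings are not independent opportunities for an AE.

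**Conclusion.** The point holds in limited form. For Visit 1, AE ascertainment and attribution rest on an unblinded judgement (explicit for ECG, inferred otherwise), and the only intensity scale cannot be applied under anesthesia or to symptom-free laboratory values. Intraoperative AE counts, grades and attribution are open to assessor bias whose direction and size the protocol does not allow one to state. Under the assumed marking rates above, the false difference is 8-18 points with 25 per arm. That shows what is possible and is not an estimate.

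The documents do not support a claim that the primary result or the raw hemodynamic comparison is compromised. The wording should be changed, but the trial's main conclusion does not turn on it.

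**What to change.** In 7.2, 8.1.2 and 8.4:

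- State that any between-arm comparison of intraoperative and PACU hemodynamic and saturation events is derived by program from the recorded 5- and 15-minute values, with analysis limits fixed before the first patient.
- Report it together with norepinephrine use. Under 5.3.2 pressure is titrated to a target in both arms during anesthesia given by unblinded staff, so events derived at that target alone would partly measure the titration.
- Keep investigator II's AE entries for reporting duties and list them as unblinded assessments.
- Grade monitor and laboratory AEs by prespecified bands of the recorded value, with AKIN stage for renal events. Keep the symptom scale for symptomatic AEs in awake patients.

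These are analysis limits only; patient management is unchanged.

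The cost is wording in three sections and a short derivation program on readings already recorded, with no added visits, staff or patients. Section 8.1.1 does not name norepinephrine among the recorded drugs, so check that the Visit 1 CRF captures it. The downside is that some brief, unimportant excursions will be counted.

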**8 Safety analyses**

**8.1 Safety measures during general anesthesia for partial nephrectomy**

**8.1.1 Administration of the study treatment**

Concentration and dosage of the study drug will be assessed for each patient:

- Measurement of the inspiratory concentration and duration of the Xe- and isoflurane-exposition.
- Determination of the exposure duration with the study drugs until the beginning of the direct tumor resection time and after the end of this, until cessation of anesthesia.
- Total amount of Xe consumption (in liter).
- General anesthesia induction dose of propofol.
- Total amount of sufentanil during the whole anesthesia.
- Total amount of rocuronium during the whole anesthesia.

**8.1.2 Clinical safety variables**

- Systolic and diastolic blood pressure and heart rate will be assessed and documented every 5 minutes from entering the operating room until discharge from the operating room and every 15 minutes in the PACU.
- ECG will be measured continuously in the operating room and PACU. Investigator II will register clinically significant ECG deviations. They will be entered in the respective adverse event section, including the severity and treatment of the AE.
- Oxygen saturation will be assessed by pulse oxymetry continuously in the operating room and PACU. It will be documented every 15 minutes.
- Investigator II will assess the respiratory variables by Felix Dual® every 15 minutes during anesthesia (FiO_2_, saturation, FeO_2_, CO_2_et, Respiratory minute volume, respiratory rate, airway pressures).
- Cuff pressure will be checked every 5 minutes during ventilation and adjusted to 25-30 cmH_2_O.
- Urine output and blood loss will be measured every hour and at the end of surgery.
- Incision-suture time, warm ischemia time corresponding to the direct tumor resection time until termination of the tumor ground-treatment, will be assessed in collaboration with the surgeons.
- Occurrence of AEs and SAEs will be assessed GCP-conform during each visit and documented in the respective section of the CRF.

**8.2  Safety measures during visit 0, 2-9**

**8.2.1 Patient safety variables and examinations**

Investigator I will assure patient safety during the inclusion visit (visit 0), the first postoperative visit (visit 2) until the end of study (visit 9). He will perform physical examinations and determine the following variables:

- Patients` vital data (blood pressure, heart rate, oxygen saturation)
- Measurement of the urine output every 6 hours until the second postoperative day and the total 24h urine output on the 2^nd^ and 3rd postoperative day.
- Acute kidney failure determination according to the AKIN classification.
- Occurrence of AEs and SAEs will be assessed GCP-conform during each visit and documented in the respective section of the CRF.

